### Study setting

This study is being conducted in two cities in Kazakhstan: Temirtau, and Almaty. These two cities are geographically distant from one another, with distinct characteristics. Almaty is the largest city in Kazakhstan (population 1,703,500) and its economic center [23]. Located close to the country’s southern border with Kyrgyzstan, it attracts both internal and external migrant workers through trade and job opportunities. Temirtau (population 181,197) is an industrial city in northern Kazakhstan [24]. The city is known for high rates of injection drug use in the years following the collapse of the Soviet Union. This study utilizes a staggered site start plan; recruitment began in Temirtau in May 2015 and in Almaty in February 2016. A project field office was established in each city where both assessment and intervention activities are conducted.

### Participant characteristics

Study participants are women who report recent histories of both drug use and sex trading. We plan to enroll a total of 350 women between the two study sites. In order to be eligible for the study, participants must: (1) be over 18 years old; (2) report illicit drug use within the past 12 months; (3) report having provided sex in return for money, goods, drugs or services within the past 90 days; and (4) report at least one incidence of unprotected sex (with either a paying or non-paying partner) within the past 90 days. Participants are ineligible if they (1) cannot communicate in Russian; (2) intend to move from the study site within the following 12 months, or (3) are deemed to have cognitive impairment that would affect their ability to provide consent or participate fully in the intervention activities.

### Intervention

All participants receive four HIVRR sessions and those assigned to the combination HIVRR+MF treatment arm receive an additional 30 sessions, including (1) six training sessions focused on financial literacy, (2) 24 sessions of vocational training in hairdressing, sewing, or manicurist professions, as well as (3) a matched savings program which incentivizes them to accumulate assets for small business development or job/vocational training. The NOVA intervention period lasts a total of 3 months post randomization, with intervention activities lasting for 2 weeks in the control arm, and for the full 3 months in the treatment arm. A brief description of each intervention component is provided below:

#### HI- risk reduction (HIVRR)

During the first 2 weeks of the intervention period, both study arms receive the HIVRR intervention. The HIVRR intervention was adapted from the Women on the Road to Health (WORTH) intervention [25]. The CDC identified WORTH as a best-practice, evidence-based intervention [26] and it has been implemented in a number of studies in the USA with women who use drugs [25, 27]. We have adapted the core components of WORTH to meet the cultural context and experience of women who use drugs and engage in sex work in Kazakhstan. The HIVRR intervention is guided by social cognitive theory [28]. It focuses on both sexual and drug use risk reduction, and is designed to increase communication, problem-solving skills, and self-efficacy related to safe-sex behaviors and drug use. Participants explore how drug use impacts their sexual risk with both paying and intimate partners, and are trained in communication skills with both. Role play activities provide the opportunity for women to practice these skills and to identify and problem-solve barriers to applying them. Participants undergo several intimate-partner violence (IPV) safety planning exercises, and regular check-ins by session facilitators ensure that women receive support and referrals if they feel that their safety is being threatened by an intimate partner or by another person during the course of the study. Participants receive basic training in emergency overdose response skills. Participants discuss informal and formal support systems available in their community. Linkage to HIV care, drug treatment (where available) and other services are provided throughout their enrollment in the study. Each session has goals setting and homework assignment that provide the opportunity for the women to practice the skills that they have learned. Participants receive HIVRR in a four-session intervention delivered twice a week for 2 weeks. Sessions are conducted in Russian by trained female facilitators and last for approximately 2 h. Participants receive small financial incentives (US$12/session) for sessions attended, as well as small safe-sex kits of condoms and lubricant.

#### Financial Literacy Training

During weeks 3 and 4 of the intervention period, the treatment arm only receives Financial Literacy Training (FLT). The FLT intervention was adapted from the financial literacy intervention used in the Undarga study [17]. FLT sessions focus on facilitating access to banking services (including how to open an account and use an ATM card), household budgeting (including development of a household budget), short- and long-term savings, debt management and financial negotiations. Sessions are designed to increase participant knowledge, skills, and self-efficacy related to managing and controlling finances, which might enhance their capacity for savings. Participants continue to build upon the goal-setting skills that they developed in the HIVRR sessions, and facilitators continue to conduct safety check-ins. Sessions are held three times per week over 2 weeks for a total of six sessions. Sessions are conducted in Russian by trained female facilitators, and last for approximately 2 h. Participants receive small financial incentives (US$12) and safe-sex kits for sessions attended.

#### Vocational Training (VT)

During months 2 and 3 of the intervention period, the treatment arm receives the Vocational Training (VT) intervention component. VT provides technical education and skills-building in a craft or trade. Including VT as a component in the HIVRR+MF intervention arm allows participants to gain competence in an employable trade, which grounds the intervention in the real world for scale-up after the trial ends. Participants in the treatment arm decide whether they wish to be enrolled in hairdressing, sewing, or manicurist vocational training sessions (dependent on course availability at each study site). Our selection of these options was informed by local feedback and a feasibility pilot conducted prior to study start, which confirmed that these were considered growing small business targets for women and that high-risk women reacted favorably to this model of vocational training. These trainings are conducted by professionals, who work either individually in the community or through a school or training program. VT partner sites were selected based on the quality of their facilities, the availability of afternoon and part-time training hours to accommodate participant schedules, and a reputation for successful graduation and certifications among students. All treatment arm participants are eligible to attend VT sessions regardless of how many FLT sessions they attended, as the material presented in the VT sessions is unrelated to the FLT. Vocational training is provided three times per week over the course of 2 months, for 24 sessions. Tuition is free to participants and women attend in small groups with only their cohort peers. Participants receive small financial incentives (US$12) for sessions attended.

#### Matched savings

From week 3 until the end of the intervention period at the end of month 3, the treatment arm receives the matched savings component of the intervention. The matched savings component of the HIVRR+MF intervention is also adapted from the Undarga program [17]. Building assets prior to shifting sources of income or moving to new or self-employment may increase the likelihood for increased income from other sources than sex work. As mentioned above, participants receive incentive payments (US$12/session) for each FLT or VT session attended. During the FLT intervention, participants receive support to open a personal savings account in a partner bank, and are encouraged to deposit their session attendance incentives in this account. Throughout the rest of the treatment intervention period, for every dollar of their incentive payment money deposited in their personal account, the project will deposit an equal amount in a separate, project-controlled account under the participant’s name. Participant’s funds will only be matched up to the total amount that they have received from incentive payments for session attendance – this limit ensures that women are not earning income through sex work for their matched savings. If a participant decides to save 100% of her incentive after every session, she will have saved a total of US$360 and would receive a matching US$360 for a total of US$720. Due to lack of documentation, lingering distrust of the banking system, or other barriers, some women may elect to never open a bank account. These participants have the option to store money with the program staff in an informal account until the time of withdrawal, and these informal accounts are also matched in a separate, project-controlled account under the participant’s name.

For a duration of 6 months after the duration of intervention sessions (until the month-9 follow-up assessment) participants may use matched savings amounts to pay for business or education expenses, including equipment and supplies for hairdressing, sewing, or manicurist professions (e.g., rental of a chair in a salon, products, fabric, sewing machines, etc.) or additional training (e.g., extra course fees). FLT intervention facilitators conduct a final “transitional session” at the end of the vocational training courses where participants are asked to set long-term goals regarding their chosen profession, and plan for spending their accrued matched savings. FLT intervention facilitators work with each participant to identify ways in which she can spend her matched savings. When a participant is ready to make a vocation-related purchase, she must provide half the amount of this purchase from her personal savings. The other half the amount of the purchase is provided by project staff from the participant’s matched account directly to the vendor or educational establishment. In order to receive this 1:1 match on their purchases, participants are required to make these purchases within 6 months of completing their vocational training (until their month-9 follow-up assessment); after this time, the project will not provide half the payment.

#### Retention sessions for control participants

As the treatment arm spends approximately 10 weeks more in the intervention sessions than the control arm, we utilize retention visits among the control cohorts to minimize a potential attentional-effect bias in favor of the treatment groups. These retention visits occur once a month for 3 months following the HIVRR intervention. Control arm participants are invited back to the field office together as a cohort, to receive small gifts (phone cards and toiletries) and to provide updated contact information to project staff. No additional training or intervention activities are provided at these retention visits, but participants are given the opportunity to interact with one another and discuss the content of the HIVRR sessions.

#### Intervention facilitators and supervision

The HIVRR and FLT sessions are led by trained study facilitators, supervised by study staff and investigators. A number of quality assurance measures have been put into place to ensure standardization across sessions and facilitators. Facilitators complete session evaluation forms after each session. Sessions are audio-recorded, and tapes are randomly selected for review by local clinical supervisors and US-based study investigators. Clinical supervisors note adherence to the intervention protocol and address any areas of immediate concern directly with the facilitators. Team supervision is held once a month with US-based study investigators through Skype calls to discuss the challenges faced by facilitators in conducting the sessions and adhering to the protocol.

### Study procedures

The study design is summarized in the Consolidated Standards of Reporting Trials (CONSORT) diagram (Fig. 2) and in the Standard Protocol Items: Recommendations for Interventional Trials (SPIRIT) schedule (Fig. 3 and Additional file 1). We expect to enroll 350 participants in the intervention over the course of 2 years, and to follow them up over 15 months post randomization. Prior studies in Kazakhstan have yielded retention rates of 88% [29]; we expect to retain 80% (*n* = 280) of participants at their month-15 follow-up assessment.

**Fig. 2 Fig2:**
[figure not shown]
Consolidated Standards of Reporting Trials (CONSORT) flow diagram

**Fig. 3 Fig3:**
[figure not shown]
Standard Protocol Items: Recommendations for Interventional Trials (SPIRIT) schedule

#### Start-up phase activities

During the start-up phase of the study, study research assistants identified a number of field locations from which to recruit potential participants. These included hotels, saunas, and other locations where sexual services are known to be offered, medical organizations such as local AIDS centers and drug treatment clinics, and NGOs providing HIV support or social services to women. Research assistants observed these sites to uncover patterns in availability of potential participants, dependent on season, day of the week, holidays, etc. During this exploratory phase, they also noted community-based “gatekeepers” who control access to potential sex workers. These not only included the NGOs and outreach workers who were our collaborating partners, but also those who manage sex work transactions in the community. While we discovered that there are very few formal “pimps” or “madams” who run official sex work establishments, sex workers in Kazakhstan often work through local hotel and sauna administrators, who direct clients to them. Research assistants described the study to these gatekeepers as a project meant to improve the health of sex workers, emphasizing the benefits of HIV and STI testing that it would provide, and asked for their help in referring potential participants when recruitment began. The relationships established through this phase reduced resistance and uncertainty from these community gatekeepers, easing later recruitment efforts.

#### Recruitment and screening

This study utilizes two channels of participant recruitment: field recruitment visits by research assistants, and network-based recruitment through a peer-referral program. Research assistants conduct regular visits to NGOs, HIV clinics, drug treatment clinics, hotels, saunas and street-based sex work venues, where they approach potential participants, provide them with a brief overview of the intervention, and then ask for their verbal consent to conduct a screening for study eligibility. To extend recruitment deeper into communities of FSW, eligible participants receive a small financial incentive (US$5) to refer their friends and acquaintances to be screened for the study. This is done through a system of paper coupons. The referred network members contact the project staff and come to the project field office location at their convenience to complete screening.

A computerized survey tool is used for eligibility screening procedures. Research assistants read the computerized questionnaire aloud to participants, asking them a number of demographic and risk-behavior questions, including those described in the eligibility section above. Participants are compensated US$1 for their time. The survey tool automatically calculates whether participants are eligible based on the responses entered by the research assistant. If participants are not eligible for any reason, they are invited to be screened again after 90 days have passed.

Eligible participants are scheduled for study intake procedures and the baseline assessment (described below) at the project field office location as soon as possible after the screening. During this baseline visit, research assistants describe the details of the study to potential participants and lead them through an informed consent process.

Research staff enroll each participant into an intervention cohort within 2 weeks of their baseline. If more than a month has passed between the participant’s baseline survey and the start of the intervention session, the participant is re-screened to confirm continued eligibility, and baseline assessments are conducted again to collect more recent data.

#### Group assignment and randomization

We enrolled participants into groups of six to eight participants each, then randomized and followed them as a cohort over time. Together as a cohort, participants are randomized to either the treatment (HIVRR+MF) or control (HIVRR) condition at the time of the first intervention session. Randomizing by cohort is more efficient than attempting to accrue enough women in a short enough period to randomize individually and simultaneously to two conditions. A random-number generator randomly assigned each cohort of participants to either the treatment or control condition. This random number generator ensured a balanced assignment of cohorts to each arm over time. Neither participants nor study staff are blind to study condition.

#### Process measures

In addition to the intervention quality control measures described above, a number of process evaluation measures are collected by the study staff to ensure fidelity and standardized delivery of study components among participants and between two diverse study sites. Among the process evaluation measures included are intervention session attendance (for both treatment and control arms), vocational training attendance (for treatment arm) and matched savings deposits and spending (for treatment arm), and retention measures. These process measures are used for a number of reasons, including supervision, assessment of standardization and fidelity to the intervention, and for use in booster training events throughout the study period.

#### Assessments

Baseline and follow-up assessments are administered by research assistants in project field office locations. Assessments take place at a pre-intervention baseline (prior to cohort assignment and randomization), then at 6, 9, and 15 months after randomization and intervention session 1 (which occur simultaneously, as participants are randomized as a cohort immediately prior to beginning the first intervention session). Since the HIVRR+MF treatment arm receives an intervention that is approximately 2.5 months longer than the control arm, we allocated an additional 2.5 months of follow-up time for in the control arm. Behavioral questionnaires are utilized at all assessments, and biological testing procedures are conducted at baseline, month-9 and month-15 assessments.

Behavioral questionnaires are conducted using computer-assisted self-interviewing (CASI) methods, with the same survey tool that the research assistants use to assess study eligibility and which can be completed in approximately 2 h. The baseline behavioral questionnaire addresses the main outcome variables of interest to the study (number of partners, number of sex acts, number of sex acts which are unprotected, number of paying partners, incidences of drug use, incidences of injection drug use and incidences of risky injection behaviors) in addition to several of the theoretical constructs underlying the study (self-efficacy in a number of risk-reduction behaviors, outcome expectancies and risk-reduction intentions) and a number of potential moderators (demographics, financial status, experience of IPV and gender-based violence (GBV), social support, linkage to care and service utilization). Table 1 contains a list of the specific measures used for each construct.

Follow-up assessments occur as early as 1 week before the exact follow-up date, and as late as 3 weeks after the exact follow-up date. Like the baseline behavioral questionnaire, the follow-up behavioral questionnaires address the main outcome variables, moderators and mediators of interest to the study. The follow-up questionnaires also include additional questions to assess how HIVRR+MF participants have utilized the vocational training and financial literacy training that they have received.

To complement self-reports and utilize an objective assessment measure of risk behavior, we use biological assays to confirm HIV and STI status. We selected five STIs: syphilis, gonorrhea, chlamydia, trichomoniasis and mycoplasma as objective proxies of sexual risk behavior. The choice of these STIs was based on their high prevalence and incidence in this population and the availability of definitive treatment with a single-dose medication (which obviates STI medication treatment adherence and compliance issues). We also selected HCV to index drug-related risk behaviors. A clinical coordinator conducts biological testing in each project field office location. A complete description of test systems used is provided in Table 2.

**Table 2 Tab2:** Biotesting systems used

Infection	Testing specimen	Test system used	Sensitivity (95% CI^a^)	Specificity (95% CI^a^)
HIV	Finger stick (whole blood sample)	Alere Determine™ HIV-1/2 Ag/Ab Combo rapid test system [47]	99.9% (99.4–100.0%)	99.8% (99.5–99.9%)
Hepatitis C (HCV)	Dried blood spot	Murex anti-HCV (version 4.0) [48]	100% (94.79-100%)	99.88% (99.77–99.94%)
Syphilis	Dried blood spot	Murex ICE Syphilis [49]	100% (99.1–100%)	100% (99.2–100%)
Gonorrhea	Vaginal specimen	AmpliSense *N. gonorrhea*/*C. trahomatis*/*M. genitalium*/*T. vaginalis*-MULTIPRIME-FRT PCR [50]	N/A^b^	N/A^b^
Trichomoniasis	Vaginal specimen	AmpliSense *N. gonorrhea*/*C. trahomatis*/*M*. *genitalium*/*T. vaginalis*-MULTIPRIME-FRT PCR [50]	N/A^b^	N/A^b^
Chlamydia	Vaginal specimen	AmpliSense *N. gonorrhea*/*C. trahomatis*/*M. genitalium*/*T. vaginalis*-MULTIPRIME-FRT PCR [50]	100% (73.3–100%)	100% (98.1–- 100%)
*Mycoplasma genitalium*	Vaginal specimen	AmpliSense *N. gonorrhea*/*C. trahomatis*/*M. genitalium*/*T. vaginalis*-MULTIPRIME-FRT PCR [50]	76.5% (50.1–93.0%)	100% (98.1–100%)

^a^CI confidence interval

^b^N/A estimates are not available for vaginal specimen samples

Participants who test positive for any STI are provided with referrals and treatment. The clinical coordinator works with individual participants to ensure that they complete their course of treatment prior to randomization and session 1, ensuring that any STI acquired post randomization is an incidence STI, and, as soon as possible at follow-up, biotesting assessments. STIs acquired and treated between the baseline and month-9 assessment or between the month-9 and month-15 assessment at an external clinic are only included as an endpoint if it is self-reported by participants on their month-9 and month-15 assessments. The clinical coordinator refers participants who screen positive for syphilis to the local Skin and Venereal Disease Dispensary to receive additional confirmatory testing for syphilis, consultations with a physician, and treatment for active forms of syphilis. Treatment for HCV is not widely available in Kazakhstan, and clinical coordinators refer participants who test positive for HCV to specialized clinics for additional examination, monitoring, and treatment. Treatment for HIV is also limited in Kazakhstan. If participants receive a positive rapid test for HIV, the clinical coordinator refers them to the local AIDS center for confirmatory testing and treatment. HIV-positive participants sign an additional waiver allowing our study access to treatment records at the local HIV clinic. Clinical coordinators collect information on confirmatory testing (for newly diagnosed cases of HIV), viral-load test results, CD4 test results, and antiretroviral (ARV) medication history at every assessment period for each participant.

Participants receive the equivalent of US$10 for the baseline assessment, US$9 for the month-6 follow-up assessment, US$11 for the month-9 follow-up assessment, and US$16 for the month-15 follow-up assessment. The total possible reimbursements for assessments is US$46.

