### Data analysis

In assessing primary outcomes (STI, HIV, and HCV incidence, unprotected sexual acts and unsafe injection acts), our over-arching modeling approach estimates intervention differences (HIVRR alone versus HIVRR+MF) longitudinally using a generalized estimating equations (GEE) approach, a flexible extension of conventional regression models, to account for repeated measures and clustering imposed by randomizing individuals in groups of six to eight women per cohort. STIs will be summarized as both a count (number of positive test results for any of the five STIs of interest (syphilis, gonorrhea, chlamydia, trichomoniasis, mycoplasma)) over the entire follow-up period, as well as a binary indicator of a positive test for any STI of interest at each follow-up time. The primary analysis will be a logistic GEE (e.g., presence/absence of an incident STI post randomization), accounting for clustering imposed by the study design in having women receiving their randomized intervention in cohorts of six to eight women each. Additionally, secondary analyses will consider intervention effects on HIV and HCV incidence as operationalized by binary indicators of testing positive for either, respectively, over the entire follow-up. We will employ logistic (binary outcomes) and Poisson (count outcomes) GEE models to estimate intervention effects as appropriate. We will implement an intent-to-treat approach for all analyses. Model estimates will be presented as estimates of incidence risk ratios or odds ratios, as appropriate, and corresponding 95% confidence intervals (CIs) and *p* values will be calculated for inference. Additionally, a logistic GEE modeling approach will be implemented for dichotomous outcomes (e.g., GEE with specified logit link) when evaluating the following outcomes: (1) self-reported unprotected vaginal and anal sexual acts with both regular and paying partners and (2) self-reported unsafe injection acts. Again, we will be interested in estimate rate ratios or odds ratios comparing HIVRR+MF to HIVRR alone. A Poisson GEE modeling strategy (e.g., GEE with specified log link) will be implemented to evaluate remaining secondary outcomes (1) self-reported number of unprotected vaginal and anal sexual acts with both regular and paying partners and (2) self-reported number of unsafe injection acts. To evaluate the secondary aims of the study related to potential moderating effects, we will expand these models to include “moderator X intervention” interaction terms along with the corresponding main effects and will assess examine the significance of each moderator on intervention effects through these interaction terms.

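### The window for externally treated, self-reported STIs opens at baseline rather than at randomization, so infections acquired in between can be scored under an endpoint defined as post-randomization

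*Protocol article*

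**What the plan says.** Two starting points appear for the same endpoint.

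- **Endpoint definition.** Assessments explains that baseline infections are treated before session 1, "ensuring that any STI acquired post randomization is an incidence STI". Data analysis describes the primary logistic GEE outcome as "presence/absence of an incident STI post randomization". Both start the clock at randomization.
- **Counting rule for outside treatment.** The next sentence of Assessments concerns "STIs acquired and treated between the baseline and month-9 assessment or between the month-9 and month-15 assessment at an external clinic". It counts these infections as endpoints on one condition, that the woman reports them at the later visit. This starts the clock at baseline.

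The two dates differ. Assessments places baseline before cohort assignment and randomization, and has randomization coincide with session 1. Recruitment and screening states: "Research staff enroll each participant into an intervention cohort within 2 weeks of their baseline". Eligibility and baseline are repeated only when more than a month separates baseline from the start of the intervention. Biological testing is done at baseline, month 9 and month 15, with none at randomization.

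Two further statements bear on the point. The clinical coordinator "refers participants who screen positive for syphilis to the local Skin and Venereal Disease Dispensary", so some infections found at baseline are by design treated outside the study. And Data analysis builds its STI variables from laboratory results, including "a binary indicator of a positive test for any STI of interest at each follow-up time", without saying how a self-reported infection enters.

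**The concern.** A woman who acquires an STI after her baseline test and has it treated at an outside clinic before session 1 satisfies the counting rule at month 9. Her infection nevertheless precedes randomization and is not an incident event under the endpoint definition. The assigned arm cannot have influenced it, so such events are expected at the same rate in both arms. They add a common background to the two incidences, move the relative risk towards 1 and reduce power.

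The sample size has little reserve to absorb this. With 0.043 expected in the HIVRR+MF arm, about 6 of 140 retained women have an event (140 × 0.043 = 6.0), so even one extra event in that arm matters.

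**Working it through.** **Inputs.** From Power and sample size: incidences 0.144 (HIVRR) and 0.043 (HIVRR+MF), two-sided alpha 0.05, 80% power, ICC 0.01, 175 women per arm, 20% attrition. From Group assignment and randomization: cohorts of 6 to 8. From Recruitment and screening: a gap of 2 weeks, or up to a month.

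**1. The plan's own figure.** The two-proportion formula with pooled variance under the null and no continuity correction is

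n = [1.96·√(2·p̄·(1−p̄)) + 0.8416·√(p₁(1−p₁) + p₂(1−p₂))]² / (p₁−p₂)²

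With p̄ = 0.0935 this is (0.807 + 0.341)² / 0.101² ≈ 129.2, so 130 per arm. Multiplying by 1 + (m−1)·0.01 and dividing by 0.80 gives totals of 344 (m = 6), 346 (m = 7) and 350 (m = 8). The stated 350 is reproduced. It follows from 0.144 versus 0.043, whose ratio is 0.299, so those incidences are used below rather than the stated relative risk of 0.25.

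**2. Power with the window opened at randomization.** Women retained per arm: 175 × 0.80 = 140. Design effect at m = 7: 1.06. Effective size: 140/1.06 = 132. Power is 80.9% and the relative risk is 0.299.

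**3. Share of women acquiring an STI in the gap.** Assume the control incidence is spread evenly over 15 months (15 × 4.345 = 65.2 weeks): f = 1 − (1 − 0.144)^(gap/15 months).

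- 2 weeks: 1 − 0.856^(2/65.2) = 0.0048
- 1 month: 1 − 0.856^(1/15) = 0.0103

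**4. Effect on the comparison.** Each arm's incidence becomes p′ = 1 − (1−p)(1−f).

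| Gap | f | HIVRR | HIVRR+MF | RR | Power |
|---|---|---|---|---|---|
| none | 0 | 0.144 | 0.043 | 0.299 | 80.9% |
| 2 weeks | 0.48% | 0.148 | 0.048 | 0.321 | 78.9% |
| 1 month | 1.03% | 0.153 | 0.053 | 0.346 | 76.5% |

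In numbers of women, f × 280 is about 1.3 to 2.9 across both arms. The calculation counts every gap infection. The rule counts only those that are also diagnosed and treated externally before month 9 and then reported, so the table gives upper values for this assumed rate.

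**The case against.** Three arguments weigh against the point.

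**The sentence restricts rather than admits.** It makes self-report a necessary condition for counting an externally treated STI and need not cancel the post-randomization requirement stated just before it. Read together, an event would have to satisfy both. That reading is possible, but the sentence names its own interval and starts it at baseline. Someone deriving events from it would have no instruction to discard the first weeks. The inconsistency stands, although it may be only one of wording.

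**An effect on the primary analysis is not shown.** Data analysis refers to positive tests only. If self-reports never enter the primary variable, the dilution there is zero. This stands as a limit on the conclusion. It is also a second conflict, since Assessments calls these infections endpoints.

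**The effect is small.** This also stands. It is a few percentage points of power at most on the assumptions used, equal in both arms and towards the null.

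A reader might infer something stronger: that infections found at the baseline test, and treated outside before session 1, are themselves counted. The text does not support this. The rule requires the infection to be *acquired* as well as treated after baseline, and an infection already positive at baseline was not. What remains is a practical risk. A woman sent to the dispensary after baseline could report that episode at month 9, and no check on its date is described.

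That risk cannot be sized. Assuming that 10-50% of baseline positives misreport, with all-STI prevalence of 10% or 28%, would bring power down to between 77% and 40%. But the reporting share is invented. Only syphilis positives are stated to go to an outside dispensary, and no syphilis prevalence is given. The 28% is first introduced as the HIV figure. Those numbers should not be attached to this point.

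**Conclusion.** The point holds in a limited form. The counting rule in Assessments starts before randomization while the endpoint starts at randomization, so STIs acquired in the gap of 2 weeks to a month can be scored although they precede assignment. At the assumed control rate this adds at most about 0.5% to 1% of women per arm, moves the relative risk from 0.30 to 0.32-0.35, and lowers power from 81% to about 79-76.5%. The sample size of 350 is not itself in error on this point.

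The size rests on three assumptions: the control incidence applies before session 1 and is spread evenly over time; gap infections are independent of later ones; and self-reported infections do enter the primary outcome. The first is uncertain, because the control incidence already supposes some benefit from HIVRR and the documents give no incidence before the intervention. Misdating of infections found at baseline is a plausible additional source of false events, of unknown size.

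**What to change.** Make three changes to the endpoint text, before the outcome is derived:

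1. In Assessments, start the first window for externally treated STIs at randomization/session 1 instead of baseline.
2. State that a self-reported episode is not an event if it matches an infection already positive at the preceding study test (baseline for the month-9 report, month 9 for the month-15 report). Check this against the laboratory results that the study already holds. Match on timing as well as infection where the report allows it, so that a genuine reinfection is not discarded.
3. Reconcile Assessments with Data analysis by saying whether self-reported STIs enter the primary outcome, or only a secondary or sensitivity version of it.

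The cost is a sentence or two of definition, a small record check, and possibly a slightly lower event count.
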